In step one of the IM protocol, the logic model of the problem was created (see Figure 2). Here, the needs of students to cycle to school daily were assessed using a concept mapping study (17). In total, 136 students aged 12–15 years attending grade 7 or 8 at three different secondary schools of different educational levels located in different sub(urban) regions in Southern Germany participated in the study. For a more comprehensive understanding of the behavior of the students, concept mapping was also performed among students' parents (*n* = 58) and teachers (*n* = 29) of both genders female and male, whereby the low retention rate of fathers did not permit a separate gender analysis. As needs to cycle to school daily, a “bicycle and related equipment,” the “way to school,” and “personal factors” were mentioned by all three analyzed samples of students, mothers, and teachers. Additionally, students mentioned “cycle training,” mothers mentioned the “role of the school,” and the teachers mentioned “storage and changing room,” “financial aspects,” as well as “information and services.” Furthermore, “social behavior in road traffic” was mentioned by girls only, “role of parents” by mothers and female teachers, and “sense of safety” by female teachers. As none of these mentioned needs stood out as particularly (un)important and/or (un)feasible, we treated all of them as equally relevant. In this study, almost all students owned a bicycle (girls: 87.8%, boys: 100%) and all were able to cycle (5). When examining the habits of the students in cycling to school, we found that approximately two-thirds of students stated to sometimes cycle to school (girls: 44.4%, boys: 72.9%), of whom approximately one-third cycled to school daily (girls: 31.6%, boys: 37.3%). On average, students generally cycled to school on 2.3 ± 2.0 days per week (girls: 1.6 ± 2.0, boys: 2.7 ± 2.0). Moreover, the following correlates were identified to be negatively associated with cycling to school habits of students: (a) being a girl, (b) increasing age (mainly in girls), (c) attending an intermediate educational level in combination with a suburban region of the school, (d) attending a school located in a small town (mainly in girls) or a medium-sized town, (e) living further away from school, and (f) having parents not using a bicycle to commute to work.

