#### Sample Size Determination

The optimal sample size for our chosen study design in the main study was calculated based on a formula by Rutterford et al. (34). This formula considers the confidence level (97.5%), power (80%), variance of days per week in cycling to school at the individual level [4.1 days (5)], our estimated clinically important difference in treatment means of days per week in cycling to school at the individual level (1.75 days), number of students per secondary school (based on the mean value in our concept mapping study: 51 students), and ICC of days per week students cycled to school at school level [0.2 days (17)]. According to this formula, the required number of students per intervention condition is 231. For the planned pilot study in the first instance, 10% of the main study's calculated sample size is recommended (35, 36) (i.e., 23 students per arm).

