#### Measuring Instruments

To perform the effect evaluation of the planned intervention, several measuring instruments were chosen (see Table 4). Furthermore, the content of the process evaluation was defined.

**Table 4 T4:** Measuring instruments for the effect evaluation.

**Outcomes**	**Variables**	**Instruments**	**Descriptions**
Primary outcome	Mode, frequency, and duration of ACTS	Two valid self-report questions (37)	Behavior of cycling to school will be measured retrospectively for 5 weekdays: (a) Thinking about the last school week, how did you get to school/home from school each day?. Possible answers are walking, cycling, car, motorcycle, bus, underground/train/tram, or other. (b) Write beside the mode the journey start and end time.
Secondary outcome	Total MVPA in min per day	Accelerometers (ActiGraph wGT3X-BT)	On 7 consecutive days (38, 39), thigh-mounted (40) accelerometers with a sample rate of 30 Hz should be worn from waking up until going to bed except during water activities for a minimum of 8 h on a minimum of 3 weekdays and 1 weekend day (38, 39). Collected data will be downloaded using an epoch length of 1 s (38, 39). For wear time validation, the algorithm from Choi et al. will be applied (41). For data analysis, cut points from Hänggi et al. will be applied (42). For initialization and data processing of accelerometers, ActiLife will be used.
Moderators	Sociodemographic characteristics (5, 20)	Thirteen self-report questions	(a) Age/grade (b) Gender (c) Bicycle ownership/roadworthiness (d) Ability to cycle (e) Shortest distance from home to school by bicycle using Google Maps (43) (f) Zip code of the school (educational level, region) (g) Subjective socioeconomic status using the reliable “MacArthur Scale of subjective social status—youth version” (44) (h) Parents' restriction/allowance in terms of letting their child cycle to school (i) Family car ownership (45)
	Daily weather conditions (46)	Meteo Info	(a) Average rainfall in l/m^2^ (b) Average wind speed in km/h (c) Relative humidity in % (d) Temperature in °C (average, minimum, maximum)

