#### Statistical Analysis

To analyze the effectiveness of our intervention, a multiple group analysis considering the treatment factor (IG vs. CG) will be performed in a structural equation modeling using *R*. In this analysis, variances in the number of cycling days to school and MVPA due to belonging to different secondary schools will be considered in the following four levels: (a) repeated measurements for each student, (b) students, in which the repeated measurements are nested, (c) the class, to which each student belongs, and (d) the school, in which classes are nested. Subsequently, potential moderators (e.g., sociodemographic characteristics of the students) will be added to the model, and cycling to school will be regressed onto potential mediators (i.e., autonomy, competence, and relatedness) in levels (b–d). Furthermore, gender will be considered as a covariate in the analysis.

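### Known predictors of cycling are used neither in allocating about ten schools nor as covariates in the first effectiveness model; one allocation stratum and student-level distance would use them cheaply

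*Protocol article*

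**What the plan says.** All places are in the protocol article.

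- **Allocation (Study Design).** The main study randomises schools by flipping a coin, with five schools and about 255 students per arm. No stratification or matching is named. The pilot is not randomised.
- **Effect model (Statistical Analysis).** Effectiveness is analysed in a multiple-group structural equation model (intervention versus control) with four levels: repeated measurements, student, class and school. Potential moderators, with students' sociodemographic characteristics as the example, are added to the model in a subsequent step. The section closes: "Furthermore, gender will be considered as a covariate in the analysis".
- **Known correlates (Logic Model of the Problem).** Factors negatively associated with cycling to school include "c) attending an intermediate educational level in combination with a suburban region of the school" and "e) living further away from school", as well as town type.
- **What is collected (Table 4).** The sociodemographic moderators include "e) Shortest distance from home to school by bicycle using Google Maps" and the school's zip code, which supplies educational level and region.
- **Discussion.** The authors say that they will control for potential mediators and moderators. They do not say which model gives the primary estimate.

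**The concern.** With about ten randomised units, two tools limit the damage from an unlucky draw: restricting the randomisation, and adjusting for strong predictors in the primary model. The plan uses neither for the predictors its own preparatory study found. Gender, the one named covariate, varies mainly within classes, so it can explain little of the variation between schools. That variation dominates the precision of the comparison.

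The sample is meant to be mixed. The limitations and conclusions in the Discussion refer to intermediate and high educational levels and to municipalities of different degrees of urbanisation. A chance excess of one school type in one arm is therefore a realistic event. There is also an ambiguity: an effect estimate before the moderator step and one after it are both possible, and the text does not say which is primary.

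**Working it through.** **1. Inputs (Sample Size Determination, Study Design).** Variance 4.1; difference 1.75 days; ICC 0.2; 51 students per school ("based on the mean value in our concept mapping study: 51 students"); power 80%; the 97.5% confidence level read as the normal quantile 1.96, i.e. two-sided 5%; five schools per arm.

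**2. The plan's own figure.** n per arm = 2 × (1.96 + 0.84)² × 4.1 / 1.75² × [1 + (51 − 1) × 0.2] = 21.016 × 11 = 231.17 (unrounded quantiles). The stated 231 reproduces, with no covariate term. It neither needs nor assumes adjustment.

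**3. Where the imprecision sits.** Between-school variance = 0.2 × 4.1 = 0.82. Within-school variance = 3.28. Variance of a school mean = 0.82 + 3.28/51 = 0.884, of which 0.82/0.884 = 92.7% is between schools. A covariate acting only within schools has little to work on.

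**4. Chance imbalance in school type.** Assume five schools of each educational level; the documents do not give the mix. An exact five-to-five draw has C(10,5) = 252 outcomes. A split of 4:1 or 5:0 in either direction has probability 2 × (1 + 25)/252 = 52/252 = 20.6%. An unconstrained coin does not even guarantee five per arm.

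**5. What a stratum costs or gains, for a post-only comparison.** This is not the planned model; it shows direction and rough scale only. SE = √(2 × (0.82 × (1 − R²) + 3.28/51)/5), with noncentral t power at 1.75 days. R² is the share of school variance explained, which is assumed throughout.

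| R² | no school term, 8 df | one school-level term, 7 df | three school-level terms, 5 df |
|---|---|---|---|
| 0% | 73.2% | 71.4% | 65.6% |
| 25% | – | 82.0% | 76.5% |
| 50% | – | 92.9% | 89.0% |

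One term breaks even when it explains about 4% of the school variance (73.0% at 7 df against 73.2%). With two terms (6 df) break-even is about 10% (73.1%). With three it is higher still, and at 0% they lose 7.6 points.

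**6. What the pre-measurement may already do.** If school means at pre and post correlate 0.5 or 0.7 (assumed), covariance adjustment multiplies the variance by 1 − 0.5² = 0.75 or 1 − 0.7² = 0.51. Power is then about 83% or 94% (7 df) before any school-type term. The 73.2% in step 5 is therefore not the power of the planned analysis.

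**7. Student-level distance.** It spends almost no school-level degrees of freedom. If it explains 20% or 50% of the within-school variance (assumed), post-only power moves only from 73.2% to 73.8% or 74.7%. Its main value is to correct for arms that differ by chance in distance.

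**The case against.** The strongest reply is that the plan does not adjust for gender alone. The sentence before the one on gender adds moderators to the model. Table 4 counts distance, educational level and region among them, and the Discussion says that moderators will be controlled for. A reader might infer from the word covariate that these variables are ignored, and the documents do not support that. What remains is the order: they come after the effectiveness model, and the primary estimate is not tied to either step.

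The second reply is that the repeated measurements include a pre-measurement. School type is fixed over five months and distance largely so, so their stable effect is already present at pre. A reader might infer that a chance imbalance passes in full into the difference between arms, or that the school variance is left wholly unexplained. Neither follows. Bias would remain to the extent that school type or distance alters the change from fall to spring. That is plausible but not documented.

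The third reply is that school-level terms are expensive with ten schools and may lose power. That is correct, and it limits the remedy to one such term. The correlates also come from only three schools, and the documents give no share of variance explained.

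Finally, details of this kind often sit in a separate analysis plan. Here, however, the article itself fixes the unstratified coin flip, the sequence of models and the named covariate.

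**Conclusion.** The point holds as a modest improvement to design and analysis, not as an error in a stated figure. Allocation without strata over about ten schools is a weak choice when a relevant school-type factor is known before the draw. Gender is also a poor choice as the only named covariate when distance is collected and known to matter.

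The size of the loss cannot be fixed from the documents. The 20.6% probability of a 4:1 or worse split assumes five schools of each educational level and an exact five-to-five draw. The power figures rest on assumed shares explained and leave out the pre-measurement. A reader might take them to show that the trial is underpowered for want of covariates. They do not show that, and the 231 per arm does not depend on adjustment.

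**What to change.** For the main study:

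1. Replace the coin flip by a balanced draw of schools within one pre-specified school-type factor, for example educational level, and include that factor in the analysis.
2. Put student-level home-school distance, measured at pre, beside gender in the primary effect model, and state that this model gives the primary estimate.
3. Keep the moderator analyses as a separate, later step.
4. Do not add further school-level terms, such as school-mean distance or a multi-class region, to the primary model.

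The cost is some wording and a stratified draw; no new data or schools are needed. The stratum takes about one of eight school-level degrees of freedom. If school type explains almost none of the school variance, power falls slightly (73.2% to 71.4% in the post-only illustration). The school type must be known for all schools before the draw.

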## Discussion

This study protocol describes the systematic planning process and design of the 5-month school-based ACTS intervention in Germany aiming to promote cycling to school among 12- to 15-year-olds. It used IM and a combination of the social–ecological model and the self–determination theory.

The decision to publish the detailed process of how our intervention was planned can be seen as a major strength as we demonstrate transparency of our structured procedure for other intervention planners. To the best of our knowledge, this is the first time that IM was used to plan an intervention aimed at the promotion of cycling to school. Our planned intervention has also several strengths: We chose the school setting for our intervention because it is regarded as ideal (50–53). According to the “Standing Conference of the Ministers of Education and Cultural Affairs” in Germany (54), the task to provide mobility and traffic education is assigned to schools, which we support with our planned intervention. Our intervention will contribute to closing the currently existing research gap by focusing on secondary schools where ACTS, especially cycling to school, is currently the least implemented activity (10) and generally, in an early development stage (9) with a lack of evidence for effectiveness in the majority of existing school-based interventions (11). We decided to focus on the promotion of cycling to school in winter (32) among the high-risk ACTS group of 12- to 15-year-olds (55) attending grade 7 or 8 (11) to expand the current state of research. As recommended, we chose a whole-of-school approach (56), a multi-level approach (21, 57), and a combination of objective as well as subjective measuring instruments to accurately assess the PA level during cycling (58). To prevent negative experiences on-road (e.g., accidents), we will first provide some theoretical and practical components off-road. Instead of choosing a top-down approach, we partly chose a participative approach to consider the opinion of the target group (i.e., students) and relevant stakeholders (i.e., parents and teachers), to address the local context appropriately, and to ensure the feasibility of the implementation of the intervention. The success of this approach will be controlled in the process evaluation. Furthermore, we will initiate collaborations (e.g., with the ADAC and police) free of charge and provide all necessary materials so that schools could continue the work beyond the duration of the intervention, which will ensure sustainability. Finally, we determined the appropriate sample size for an adequately powered effect evaluation, will control for potential mediators and moderators in our analysis (57) and will pilot the intervention. The purpose of piloting is to pre-test the effectiveness, acceptance, and feasibility of the intervention, as it will later be performed in the main study, in accordance with the planned organizational procedure and chosen measuring instruments for data collection described in this study protocol but by using a smaller sample size and a weaker, that is, quasi-experimental, study design.

However, the following limitations have to be considered. In general, following the IM protocol was a time-consuming process making it difficult to fulfill each of its sub-steps (59). The time factor is also why the opinion of the target group could not be considered in every step (e.g., how students would design the intervention) but the IM protocol is normally only followed by researchers anyway (60). Besides, one demand mentioned in the needs assessment, that is, storage and changing room, could not be considered in the planned intervention. Moreover, this intervention was designed as an RCT providing a high evidence level (61) but without a follow-up. It will be characterized by a selective sample, that is, recruiting students of intermediate or high educational levels and regional restriction to (sub)urban areas in Southern Germany, and a moderate-term duration so that findings will not be generalizable.

Altogether, using the IM protocol to systematically plan an intervention is a time-consuming and complex procedure for researchers (59, 62, 63) but recommendable as it increases the chance to achieve the defined aim(s) of a planned intervention (12, 63). We suppose that the planned intervention adequately matches the needs of students aged 12–15 years grade 7 or 8 at secondary schools in Southern Germany, covering different educational levels (i.e., intermediate and high) and located in different municipalities urbanized to different levels. Thus, we expect that our effect evaluation will show increasing numbers of days on which students cycle to school and increasing total MVPA. As we considered the opinion from the target group and all relevant stakeholders in the planning process to a certain extent, we expect that the process evaluation will show satisfaction concerning components and the implementation of the intervention as intended.

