### Program Implementation Plan

For convenience, the three secondary schools included in our concept mapping study were asked to pilot the intervention. Two more secondary schools, each characterized by similar features as the already recruited ones, that is, in terms of regions, educational levels, and grades, will be searched by sending random invitation letters. Similar random invitation letters will also be sent to recruit secondary schools in the main study.

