#### Study Design

The main study is planned as a two-arm (i.e., intervention and control group (IG; CG)) three-level cluster (i.e., students in classrooms in schools) RCT (see Figure 4), whereby a simple randomization technique (i.e., flipping a coin) on school-level was chosen. For convenience, the pilot study will follow a quasi-experimental study design as a non-RCT. Directly before and after the implementation of the intervention, a pre- and post-measurement will take place as part of the effect evaluation. Furthermore, the process evaluation will take place during and after the implementation of the intervention. Based on the intraclass correlation coefficient (ICC) of 0.2 calculated for the variance of days per week students cycled to school between the three secondary schools in our concept mapping study (17), we assigned more than one secondary school to the IG and CG. No treatment will be delivered to the CG. In the main study, approximately 255 students belonging to five schools with two classes in grade(s) 7 and/or 8 will be in the IG and CG, respectively. However, approximately 150 students belonging to three schools will be in the IG and 100 students belonging to two schools in the CG when piloting the intervention.

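### The pilot is meant to pre-test effectiveness, but a non-randomised comparison of three schools with two cannot reliably separate an effect from school differences

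*Protocol article*

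**What the plan says.** The Discussion sets out what the pilot is for: "The purpose of piloting is to pre-test the effectiveness, acceptance, and feasibility of the intervention". The same sentence concedes that this will be done "by using a smaller sample size and a weaker, that is, quasi-experimental, study design".

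Study Design gives the form: "For convenience, the pilot study will follow a quasi-experimental study design as a non-RCT". It adds that "approximately 150 students belonging to three schools will be in the IG and 100 students belonging to two schools in the CG". The same section cites a school-level ICC of 0.2 as the reason for having more than one school per arm.

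On recruitment, the Program Implementation Plan says: "For convenience, the three secondary schools included in our concept mapping study were asked to pilot the intervention". The others are described as "Two more secondary schools, each characterized by similar features as the already recruited ones", with similarity judged on region, educational level and grade.

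Statistical Analysis describes one effectiveness analysis, a multilevel model comparing the intervention group (IG) with the control group (CG). It has no separate, descriptive-only treatment for the pilot. Ethics and Dissemination foresees journal publication of both the pilot and the main-study findings.

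**The concern.** Taken together, these sections lead to a published between-arm comparison on effectiveness from five schools that were not randomised. Two problems arise.

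- **Imprecision.** The unit that varies is the school. With three schools against two, 3 degrees of freedom remain for the contrast, and measuring more students per school barely helps.
- **Bias.** Allocation is by convenience. The Logic Model of the Problem reports that the three concept-mapping schools differ in educational level and region and that these features are associated with cycling to school. Two control schools cannot be matched one for one to three different intervention schools, so selecting on similar features gives only partial balance.

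At stake is how the pilot result will be read. A difference due to chance or selection could be published as early support for the intervention, or a null result could be taken as evidence against it. The pilot can inform acceptance and feasibility without an effectiveness claim.

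**Working it through.** **Inputs from the protocol.** Sample Size Determination gives variance 4.1, target difference 1.75 days, 51 students per school, ICC 0.2, power 80% and a 97.5% confidence level. Study Design gives about 150 students in three IG schools and 100 in two CG schools, so about 50 per school. The outcome is counted over five weekdays (Table 4).

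**Reproducing the plan's own figure (main study).**
- Unclustered n per arm = 2 × 4.1 × (1.960 + 0.842)² / 1.75² = 21.02.
- Design effect = 1 + (51 − 1) × 0.2 = 11.
- n = 21.02 × 11 = 231.2, which matches the stated 231. The stated confidence level therefore works as z = 1.96, that is, two-sided 5%.

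The protocol states no power or precision for the pilot. Its only pilot size rule, 10% of the main study or 23 students per arm, is less than half of one 51-student school (23/51 = 0.45). It gives no support for an effect comparison.

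**Pilot, post-only comparison of school means.**
- Variance of a school mean = 4.1 × (0.2 + 0.8/50) = 0.886.
- SE of the difference = √[0.886 × (1/3 + 1/2)] = √0.738 = 0.86 days.
- School variation alone gives √[4.1 × 0.2 × (1/3 + 1/2)] = 0.83 days, so nearly all of the SE comes from schools.
- Degrees of freedom = 5 − 2 = 3, and t(0.975, 3) = 3.182.
- 95% half-width = 3.182 × 0.859 = 2.73 days (1.68 with normal quantiles).
- Power for 1.75 days, noncentral t on 3 df: about 30% (53% with normal quantiles).
- With no true effect, P(|difference| ≥ 1 day) = 2 × [1 − Φ(1/0.859)] = 0.24.

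An observed difference of exactly 1.75 days would have a 95% interval from 1.75 − 2.73 = −0.98 to 1.75 + 2.73 = 4.48 days, on a 0 to 5 scale.

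**Pilot, using the baseline.** The plan measures before and after, but the protocol gives no pre-post correlation, so a range is assumed. For school-level correlation r_s and student-level correlation r_i, the variance of a school's mean change is 4.1 × [0.2 × 2(1 − r_s) + 0.8 × 2(1 − r_i)/50].

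| r_s | r_i | SE (days) | 95% half-width, 3 df | Power for 1.75 days |
|---|---|---|---|---|
| 0.5 | 0.5 | 0.86 | 2.73 | 30% |
| 0.5 | 0.7 | 0.85 | 2.69 | 30% |
| 0.8 | 0.5 | 0.57 | 1.82 | 55% |
| 0.8 | 0.7 | 0.55 | 1.76 | 57% |
| 0.9 | 0.5 | 0.44 | 1.39 | 76% |
| 0.9 | 0.7 | 0.41 | 1.31 | 80% |

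Even in the most favourable row, an observed 1.75 days would have an interval from 0.44 to 3.06 days.

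**Sensitivity to the ICC.** The ICC comes from only three schools. Post-only, an assumed ICC of 0.10 gives a half-width of 2.02 days and power of 47%; an ICC of 0.05 gives 1.55 days and 68%. A lower ICC combined with strong correlations would be tighter again, but the protocol supplies neither.

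All these figures describe chance variation between schools and students. They contain no allowance for bias from non-random allocation.

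**The case against.** There is a fair case on the other side.

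- **The weakness is disclosed.** The protocol calls the pilot quasi-experimental, weaker and a non-RCT, and pre-testing can be read as rehearsing the whole evaluation. It also ties adequate power to the calculated sample size, which belongs to the main study. This stands as disclosure. It sets no limit on interpretation, however, and the limitations in the Discussion do not mention the pilot's allocation.
- **The baseline removes stable school differences.** This stands, and it makes the post-only figures the adverse end of the range. Change that differs between schools remains, and the Program Implementation Plan itself cites large seasonal swings in cycling to school.
- **The added schools are to have similar features.** This is a partial control, for the reason given above.
- **A concurrent control arm is useful for rehearsal.** Agreed. Nothing here argues for removing it.

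A reader might go further and infer two things that the protocol does not support. One is that a misleading pilot effect would set the main study's size or decide whether it goes ahead. In fact the main-study size is already fixed from concept-mapping data and a chosen 1.75-day difference, and no go/no-go rule appears. The other is that the three concept-mapping schools are the three IG schools, so that schools that helped shape the intervention face newcomers. The matching counts and the words "the three secondary schools included in our concept mapping study were asked to pilot the intervention" suggest this, but no section says so.

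**Conclusion.** The point holds in this form: the protocol names effectiveness as a purpose of a pilot whose non-randomised comparison of three and two schools cannot reliably support it, and it plans to publish the findings. At the protocol's own inputs, the post-only 95% half-width of 2.7 days exceeds the whole 1.75-day target, and power is about 30%. With the baseline used, the range is 2.7 down to 1.3 days and 30% up to 80%. Only the most favourable assumed correlations reach the usual 80%, and selection bias and differential change come on top.

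The conclusion rests on about 50 students per school, an ICC near 0.2, a school-level t reference with 3 degrees of freedom, and correlations that the protocol does not give. The harm lies in how the pilot difference is read or published. The main study's sample size, design and analysis are not affected.

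**What to change.** In the Discussion, remove effectiveness from the stated purpose of the pilot. Limit the purpose to acceptance, feasibility, and rehearsal of the measurement and analysis procedures. State that any IG-CG difference from the pilot will be reported descriptively, adjusted for baseline, with an interval that reflects five schools, and that it is not evidence of effect.

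This is a change of wording. The control arm, the instruments and the schedule stay as planned. The price is giving up an early effectiveness claim.

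Optionally, if all five schools are willing and none is yet committed to an arm, allocate them by lot; school-level randomisation is already planned for the main study. This reduces selection bias but leaves the standard error and the 3 degrees of freedom unchanged, so it does not replace the change above. It may not be possible for schools already approached to pilot the intervention.
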